### Implementation of the WHC

Prior research suggests the need to adapt and modify evidence-based programs to make them more flexible and amenable to scale-up in real-world settings [13]. The adaptation and modification steps need to be monitored and evaluated to ensure that they support continued fidelity to the overall model and lead to outcomes that are similar, but not necessarily identical, to efficacy trials. A framework for wider scale-up that leads to adoption of an innovation in real-world settings must consider multiple, nested levels—such as patient, provider, setting, organization, and environment—at which implementation and evaluation occur [30]. The approach posits that successful implementation begins with an evidence-based practice, in this case the WHC, to which there is initial training of clinical staff followed by preliminary and setting-specific modifications, then adoption and evaluation of multilevel outcomes. The process begins with formative work to identify any potential barriers to adoption and use of the WHC. Modification, implementation, and evaluation are iterative and interactive processes that form a feedback loop for monitoring service delivery, intervention refinements, implementation strategies, evaluation protocols, and quality of care in a staged progression prior to full implementation. As part of this project, these multiple steps will be implemented to refine and test the WHC program for wide-scale use in healthcare clinics and substance use rehab centers.

## Methods

### Aims and objectives

The overarching goal of this project is to assess the acceptability and feasibility of implementing the WHC in usual care settings and to assess the effectiveness of the intervention as it is implemented. The project has three specific aims. Aim 1 is to undertake qualitative data collection to develop, implement, and assess the appropriateness of a marketing plan or a recruitment strategy to facilitate entry into HTC/healthcare clinics and substance use rehab centers for the implementation of the WHC. Aim 2 is to test and evaluate a modified WHC program that has inputs from the first phase; evaluation will use a stepped-wedge design across the health clinics that provide HTC, ART, TB treatment, and antenatal care matched with substance use rehab programs to determine implementation outcomes (appropriateness, acceptability, adoption, cost, fidelity, feasibility, and sustainability) and service outcomes (comprehensiveness of services and timely service linkages). Aim 3 will assess the impact of the WHC program on patient outcomes at 6-month follow-up.

### Setting

The WHC is being rolled-out sequentially in four HTC/healthcare clinics and four outpatient substance use rehab centers located in selected disadvantaged communities (townships) in Cape Town. These sites were identified and approved by the City of Cape Town Health Department. Each HTC/healthcare clinic was paired with a substance use rehab center based on geographic proximity, and each pair was randomized by computer into four succeeding 6-month implementation cycles where implementation of the WHC is taking place simultaneously at the paired sites.

### Study design

The overall study uses a stepped-wedge design, as shown in Fig. 1. This design lends itself to implementation science research adaptation and mixed methods [31]. It also has several logistical and scientific advantages, as it involves incremental execution of the intervention; allows continued measurement of key process and outcome indicators; accommodates periods of feedback loops; allows for retrospective evaluation of sustainability; and accounts for temporal trends, such as changes in ART regimens (i.e., universal coverage) or funding for healthcare that may impact implementation. Our iterative approach will incorporate lessons learned at each step, making the integration process more efficient and conducive to identifying aspects of the clinic environment and the WHC that are acceptable, scalable, and sustainable.

**Fig. 1 Fig1:**
[figure not shown]
Implementation science study design for the Women’s Health CoOp program

As depicted in Fig. 1, this study has 4 cycles spanning several years. Each implementation cycle of the WHC program lasts 6 months. Based on the findings from each cycle, we undertake a brief formative “lessons learned” evaluation. These periods between cycles inform backward- and forward-implementation strategies through mixed methods of brief staff surveys and focus group discussions (FGDs), allowing for modification of the WHC while preparing for training in the next cycle. Pre-, mid-, and end-of-implementation FGDs are conducted to inform the modifications, including training materials, curriculum, and implementation data collection. Pre-implementation FGDs involve setting the stage for entry into the clinics, so that barriers and challenges can be addressed. Mid-implementation FGDs explore initial results and help determine if additional modifications to the intervention are needed. End-of-implementation FGDs with clinic staff and patients explore satisfaction with the intervention and concerns with the program’s sustainability. This format provides back-and-forth feedback and dialogue with clinic staff on the implementation processes and outcomes for further refinement. Consequently, the clinics randomized to Cycle 1 will have the longest post-intervention observation period, with implementation sustainability measured through fidelity checks and quantitative surveys. Conversely, based on lessons learned throughout the earlier cycles, sites in Cycle 4 benefit from an intervention that is more refined and in the most scalable form.

### Study procedures

#### Data collection: formative phase

The formative phase was completed in November 2014. During this phase, we engaged our Community Collaborative Board (CCB)—a group of key stakeholders and policymakers that have been key collaborators on the CoOp studies in South Africa since 2003, staff from the local department of health, and women who use substances from the target communities—to develop a marketing plan and engagement strategy that addressed the potential challenges and barriers to integrating the WHC into existing HTC/healthcare clinics and substance use rehab centers in Cape Town. These informants helped identify potential challenges to integrating the WHC into usual care settings. Methods of engagement included expert interviews with regional and local policymakers and FGDs with staff from HTC/healthcare and substance use rehab centers. Information from the formative phase led to important adaptations to the WHC model. In particular, we were able to identify the need to implement extensive recruitment strategies in the community because many of the women who were living with HIV and using substances were not currently visiting health facilities [32].

#### Data collection: implementation phase

We are using a Type 2 hybrid trial design that emphasizes both clinical effectiveness and implementation outcomes, with the eventual goal of more rapid translation and uptake to usual care settings [33]. Consequently, data collection will include repeated measures at the clinic and patient levels.

### Clinic-level data collection

Prior to integrating the modified WHC program into the facilities, clinic staff are identified and presented with information on the WHC intervention. They then complete a survey to assess organizational readiness for change, including perceived barriers to change, acceptability, feasibility, and appropriateness of implementing the WHC in these facilities. This survey is then re-administered at the end of the implementation cycle. This process will be repeated at subsequent cycles. To assess long-term sustainability of the WHC, we will complete a brief checklist 6 months after the end of each cycle. These post-intervention sustainability checks will be repeated after each cycle such that Cycle 1 facilities have the longest post-intervention observation period on sustainability.

### Patient-level process and data collection

The patient-level study includes a baseline visit and a 6-month follow-up visit to evaluate intervention effectiveness. Eligibility criteria include (1) being between the ages of 18 and 45 years, (2) self-reporting use of at least one drug, including alcohol, at least weekly during the previous 3 months, (3) reporting unprotected sex with a male partner in the past 6 months, (4) having a positive verifiable HIV test result, (5) reporting the intention to remain in the area for at least the next 6 months, (6) providing contact information, and (7) being willing to participate in alcohol and other drug screening.

A field team hired by Kheth’Impilo, the local nongovernmental implementing partner, leads the outreach and data collection activities. Trained outreach workers operate as recruiters of women within clinics and surrounding communities and track eligible women for the study, while data capturers collect patient-level data from participants at the baseline and 6-month follow-up appointments. These are well-established methods from other studies conducted in the region [34, 35]. Once participants are enrolled, clinic staff trained and certified in the WHC offer the adapted intervention to all women enrolled and to other women in their clinics who may be interested in participating, so as to operate as a real-world setting.

At each data collection visit, a member of the research/implementing team administers a face-to-face interview using a secure tablet with skip patterns and quality-control checks programmed into the interview. The study instrument includes measures of socioeconomic status, sex risk behaviors, AOD use, substance abuse treatment readiness, ART use and barriers to use, and other self-reported clinical outcomes such as TB and symptoms for sexually transmitted infections. Biological data are obtained from a urine specimen tested for pregnancy and metabolites for recent drug use. Participants also undergo a breathalyzer test for recent alcohol use. The same measures are collected at 6-month follow-up.

HIV testing is not part of the research because it is performed by clinic staff as part of standard clinic operations. As proof of HIV-positive status, participants must provide a clinic-issued document such as an antiretroviral (ARV) card or ARV medication with identifiable data linking to the participant, or they must consent the research staff to access their hospital records for their results. Viral load is also collected at baseline and 6-month follow-up from the South African National Health Laboratory Service (NHLS) database in the clinics. Viral load testing is also part of the standard of care and the clinics routinely perform HIV viral load testing 6 months after a patient begins taking ART and then 12 months later; however, these intervals may vary by clinic. Viral load test information will be used to validate self-reported ART adherence.

In each cycle, the objective is to enroll 120 women (60 from a HTC/healthcare clinic and 60 from a substance use rehab center) for a sample total of 480, and to follow each enrolled participant at 6 months, with an expected follow-up rate of 90%. At the end of the 6-month follow-up period, we will assess effectiveness of the program using pre-post comparisons to determine whether women reduced their AOD use, are adhering to their ARV regimen, have reduced their sex risk behaviors (e.g., using a condom at every sex act; less transactional sex), and have experienced less to GBV. At the end of each cycle, we will conduct FGDs with a subsample of women who participated in both workshops of the intervention and completed their 6-month follow-up appointment. These study activities will enhance our understanding of women’s satisfaction with the WHC program and suggest modifications to the program for broader acceptability and implementation that will be incorporated into the next cycle.

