To assess effectiveness, the analysis will compare changes from baseline to 6-month follow-up on the amount of alcohol consumption, biological and self-reported drug use, condom use at last sex, number of sex partners over the past 6 months, and values from scales that measure relationship power and communication. We will start with descriptive analyses, including measures of central tendency, and dispersion (e.g., means, medians, proportions, standard deviations). Bivariate analysis will include paired t-tests, Wilcoxon rank-sum, and tabular statistics and the chi-square test. For multivariable analysis, the xtlogit and xtgee function will be used to specify random effects or fixed effects, and will assume that the correlation matrix is exchangeable. The models will control for other covariates identified in bivariate analyses or hypothesized a priori (e.g., condom use is correlated with substance use). One of the most important covariates in the model will be measures of patient satisfaction. Model performance and fit will be assessed with incremental elimination of variables, likelihood ratio tests, and changes in the Akaike information criterion (AIC) and Bayesian information criterion (BIC) values.

Patient satisfaction analyses will be predominately descriptive to determine if satisfaction improves with each cycle, varies by type of clinic, and by participant characteristics (e.g., alcohol use, pregnancy status).

We assume that the prevalence of patients receiving or adhering to ART or receiving treatment for substance abuse are Poisson distributed and increase from baseline to follow-up. We will use a similar approach outlined in the effectiveness analysis for bivariate and multivariable analyses. Variables considered for multivariable analysis will include patient characteristics, measures of patient success with the WHC, patient satisfaction, and clinic-level characteristics (e.g., type of clinic, provider satisfaction).

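### Entry criteria select women on AOD use and unprotected sex, so uncontrolled pre-post change in these behaviours should show some improvement even if the WHC has no effect

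*Protocol article*

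**What the plan says.** Two of the seven eligibility criteria in Patient-level process and data collection are behavioural. One is "self-reporting use of at least one drug, including alcohol, at least weekly during the previous 3 months"; the other is "reporting unprotected sex with a male partner in the past 6 months". Clinic staff then "offer the adapted intervention to all women enrolled". On timing, "The patient-level study includes a baseline visit and a 6-month follow-up visit to evaluate intervention effectiveness", so each woman is measured once before and once after.

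The same section states the test: "we will assess effectiveness of the program using pre-post comparisons to determine whether women reduced their AOD use". It gives examples of lower sex risk: "using a condom at every sex act; less transactional sex". The Analysis section lists the effectiveness measures: "the analysis will compare changes from baseline to 6-month follow-up on the amount of alcohol consumption, biological and self-reported drug use, condom use at last" (that is, at the most recent act). It adds number of partners and scales for relationship power and communication. It names paired t-tests among the bivariate methods.

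The Study design section says that the stepped wedge accounts for temporal trends, and the Analysis section lists time among the factors that can affect outcomes. The article does not mention regression to the mean, and it describes no women who meet the same criteria and are followed for 6 months without exposure.

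**The concern.** The behaviours that qualify a woman for entry overlap with those used to judge success. Women enrolled because a fluctuating, self-reported behaviour was recently at a risky level will, on average, report a somewhat less risky level later, whatever is done in between. A pre-post test credits that drift to the WHC.

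The stepped wedge does not remove it. Site pairs are randomized to cycles, but within each cycle every pre-exposure observation is taken just after selection and every post-exposure observation 6 months later. The shift follows each woman's own selection date, so adjustment for calendar time leaves it in place.

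At stake is Aim 3, the impact of the program on patient outcomes. AOD use and condom use make up much of the effectiveness list, so an inert program could appear to work on those measures.

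**Working it through.** **The plan's own figures.** The Power section gives detectable differences of 4% for mean adherence (SD 17.28) and 13% for the proportions adherent (56%) or suppressed (55%). I used the Hussey and Hughes variance with 4 clusters, 5 periods, 240/5 = 48 observations per cell and between-cluster variance 0. Two-sided alpha 0.05 is assumed, as neither alpha nor an ICC is stated. Summing the exposure indicators gives U = 10 and W = 30, so Var = 4(σ²/48)/(4 × 10 − 30) = 0.4σ²/48.
- Mean: 2.80 × √(0.4 × 17.28²/48) = 4.42 points.
- Proportions: 12.7 points at both 56% and 55%.

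These agree with the stated 4% and 13%. They concern outcomes that are not entry criteria. The article gives no corresponding figure for AOD or condom use.

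**Outcome that repeats a criterion.** Followed pairs: 480 × 0.90 = 432. If the item has the same recall window as the criterion and the baseline answer agrees with the eligibility answer, no woman can be a consistent condom user at baseline. All discordant pairs then point to improvement. With k changers, the exact two-sided McNemar P is 2 × 0.5^k. For k = 5 this is 0.0625; for k = 6 it is 0.031. Six women are 6/432 = 1.4%.

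**Score cut at the entry threshold, no WHC effect.** Take a standard normal score in the source population. A share q exceeds the threshold z, and the correlation between visits is r. The expected fall among selected women is (1 − r) × φ(z)/q. The documents give neither q nor r, so both are assumptions.

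| q | φ(z)/q | r = 0.8 | r = 0.4 |
|---|---|---|---|
| 0.50 | 0.798 | 0.16 SD | 0.48 SD |
| 0.70 | 0.497 | 0.10 SD | 0.30 SD |
| 0.85 | 0.274 | 0.05 SD | 0.16 SD |

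**False-positive rate.** Same model, 432 pairs, paired test, 2,000 simulations. The nominal rate in the direction of improvement is 2.5%.

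| q | r | No longer meets criterion at 6 months | Significant improvement |
|---|---|---|---|
| 0.5 | 0.7 | 25% | 100% |
| 0.5 | 0.9 | 14% | 96% |
| 0.7 | 0.7 | 16% | 99% |
| 0.7 | 0.9 | 9% | 66% |
| 0.9 | 0.7 | 6% | 38% |
| 0.9 | 0.9 | 3.5% | 15% |

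Both tables describe a score on which selection acts directly. An outcome only correlated with that score would be expected to shift less.

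**The case against.** A reader might infer that all AOD and sex-risk outcomes are fixed at their worst value, that the test rejects almost surely under no effect, and that a positive result carries no information. The documents do not support this.

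- No outcome on the Analysis section's list is fixed by entry. A weekly drinker can drink more, a woman who used a condom last time may not next time, and partner numbers can rise.
- Weekly use as a yes/no endpoint is never named. A condom at every act appears only as an example, without a recall window, and an article may leave item definitions to the full protocol.
- The drug criterion is met by any one substance, so alcohol amount is not directly selected in women who qualified on another drug. Number of partners and transactional sex are not entry criteria.
- If most source women meet the criterion and behaviour is stable, the bias is small: at q = 0.9 and r = 0.9 the false-positive rate is 15%.
- The powered outcomes are not selected on, and the criteria describe the women the WHC is meant to reach.

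All of this stands and limits the point's reach and size. It does not remove the point. The overlap between criteria and outcomes is in the text, no unexposed comparison is described, and every scenario tried exceeds the nominal rate.

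**Conclusion.** The point holds in limited form. Selection on recent AOD use and unprotected sex, followed by an uncontrolled pre-post comparison, biases change in AOD use and condom use towards apparent improvement. Only an outcome that repeats a criterion over the same window is unable to worsen; there, 1.4% of women changing is enough for P = 0.031.

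For related outcomes the direction is predictable but the size is not determined by the documents. The working gives 0.05 to 0.48 SD (assumed q 0.5-0.85, r 0.4-0.8) and false-positive rates of 15% to 100% (assumed q 0.5-0.9, r 0.7-0.9). These ranges show what is plausible under a simple model and are not estimates for this trial.

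ART adherence and viral suppression are not directly biased by this mechanism. The matter should be fixed, but it does not undermine the powered outcomes through selection.

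**What to change.** In Patient-level process and data collection and in Analysis:

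1. Report any outcome that repeats an entry criterion descriptively, without an effectiveness test.
2. Label AOD and condom results as change from baseline, not as a WHC effect. Show beside them the regression-to-the-mean shift over a stated range of assumed prevalence and reliability.
3. Do not rest the Aim 3 impact statement on these outcomes.
4. State that adherence, suppression, GBV and relationship power avoid this selection bias but remain uncontrolled pre-post comparisons. Moving the impact claim to them does not by itself make it causal.

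The cost is wording and one small table, with no new data and no change to eligibility. The downside is that fewer outcomes can support an effectiveness claim. These steps disclose the bias without removing it. Removal would need women enrolled under the same criteria and followed unexposed, for example at sites not yet in their cycle. That would be a larger change for a study already in the field.

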In this article, we describe the protocol for a study funded by the U.S. National Institute on Alcohol Abuse and Alcoholism to assess the feasibility and acceptability of implementing an evidence-based, gender-focused intervention—the Women’s Health CoOp (WHC) program—in government health clinics that provide HIV testing and counseling (HTC), ART, tuberculosis (TB) treatment, and antenatal care; and in substance use rehabilitation (rehab) centers in South Africa. The project also assesses the effectiveness of the WHC among the women participants and the sustainability of the program in these settings over time.

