### Power

We used the Stata command, *steppedwedge* [36], which is based on the equation developed by Hussey and Hughes [37] to calculate the detectable difference between participants’ adherence before and after their exposure to the intervention, given a sample size that is feasible and realistic in these clinic settings (*n* = 480; or 120 participants per cluster). We conducted two analyses based on the following parameters: 120 participants per cluster, 240 observations per cluster, and power of .80. The first analysis was used to calculate the detectable difference between participants’ self-reported percentage of ART adherence during the past month before and after the intervention. No previous research has estimated the percentage of ART adherence among South African women who use substances since the government approved the provision of ART to all people living with HIV, regardless of CD4 count. Consequently, we based our analyses on a national estimate of the average percentage of ART adherence in South Africa since the ART rollout (87%; SD = 17.28). Based on this estimate, we will be able to detect an increase or decrease in adherence of 4% or greater. Next, we calculated the detectable difference between the proportion of adherent (i.e., report 95% or greater adherence or are virally suppressed) participants before and after their exposure to the intervention. We based this calculation on previous research that has reported on the proportion of people who engage in substance use that are adherent to ART (56%) [38] and national estimates indicating that 55% of all people living with HIV are virally suppressed [39]. In regards to self-report adherence, we estimate that we will be able to detect a difference of 13% or greater. Similarly, we also estimate that we will be able to detect a difference of 13% or greater to examine the change in the proportion of women who are virally suppressed before and after the intervention.

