### Analysis

The analysis will treat count outcomes as Poisson distributed. A number of multilevel factors can impact the outcomes, including site/clinics, city, time, and the type of the site (HTC vs. substance use rehab). Because individuals are clustered within sites and sites are clustered within a city, we need to consider the variance inflation factor that results in this clustering. We considered a number of approaches: using random effects, fixed effects, or Generalized Estimating Equations (GEE) considering population-averaged methods. Although a random effects model for sites seems a natural approach, we needed to consider fixed effects of the city and of the site type, which would leave little power left to estimate the random effects distribution. Consequently, we will also use two other methods, GEE and the fixed effects model, to assess sensitivity by comparing the results across these models.

We will use Stata Release 14 (College Station, TX) and SAS version 9.2 (Cary, NC). Data will be examined to determine the extent to which they meet appropriate distributional assumptions. We will use methods described by Ecob and Der to identify outliers in longitudinal models and use methods of case downweighting when extreme cases are identified [40]. Missing data will be handled using multiple imputation methods [41]. The patient-level analyses will be organized into three groups to examine (a) successful reduction of risk behaviors targeted by the WHC (i.e., effectiveness), (b) patient satisfaction, and (c) increasing the number of women receiving ART and adhering to ART, and being admitted to substance use rehab.

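### Women can enter at HIV diagnosis in clinics that test and treat, so routine ART starts form part of any pre-post rise in ART outcomes and cannot be separated from a WHC effect

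*Protocol article*

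**What the plan says.** All references are to the Protocol article.

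- **Entry.** Under Patient-level process and data collection, the HIV criterion is "having a positive verifiable HIV test result". An ARV card or labelled ARV medication serves as proof of status, "or they must consent the research staff to access their hospital records for their results". A woman who has never taken ART can therefore qualify.
- **Where women come from.** The same section says: "Trained outreach workers operate as recruiters of women within clinics and surrounding communities". Each cycle takes 60 of its 120 women from an HTC/healthcare clinic. The Background describes these sites as "government health clinics that provide HIV testing and counseling (HTC), ART, tuberculosis (TB) treatment, and antenatal care".
- **Standard care.** "HIV testing is not part of the research because it is performed by clinic staff as part of standard clinic operations". The Power section refers to the period since "the government approved the provision of ART to all people living with HIV, regardless of CD4 count".
- **Comparison.** Women are measured at baseline and 6 months, all enrolled women are offered the WHC, and effectiveness is judged pre-post.
- **Outcome.** The third group of patient-level analyses in the Analysis section concerns "increasing the number of women receiving ART and adhering to ART", together with admission to rehab. That section assumes these prevalences go up between the two visits.
- **Stated protection.** Study design says the stepped wedge allows for time trends, and gives universal ART coverage as an example.

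**The concern.** A woman enrolled at or soon after her positive test is off ART at baseline because her care has only just begun. Under a treat-all policy, the clinic's ordinary process should start many such women on ART within the next 6 months, with or without the WHC. In a pre-post comparison without untreated women, each routine start counts as improvement under the WHC.

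This is not a calendar trend. It follows each woman's time since diagnosis and recurs in every cycle. ART uptake and adherence carry the trial's link to the 90-90-90 goals, so a significant rise in them is likely to be read as an effect of the WHC.

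**Working it through.** **Inputs from the article.** 480 women with 90% followed, so 480 x 0.90 = 432; 56% adherent (Power); detectable differences of 4 points for mean adherence, and 13 points for the proportion adherent and for the proportion suppressed (Power).

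**Assumed inputs, not in the article.** f = share of women newly diagnosed and off ART at baseline, 5-30%. s = share of those who start ART in routine care by 6 months, 50-90%. The WHC effect is set to zero.

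**1. The plan's own figures.** I used the Hussey-Hughes variance with 4 clusters, 5 periods and 240/5 = 48 observations per cluster-period, two-sided alpha 0.05, power 0.80 and ICC 0. Alpha, ICC and the number of periods are assumed. This gives 4.4 points for the mean (SD 17.28) and 12.7 points for both 56% and 55%, which round to the stated 4, 13 and 13. An ICC of 0.01-0.20 gives 5.1-5.4 and 14.6-15.6 points. The 13 points apply to the proportion adherent or suppressed, not to the proportion receiving ART.

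**2. Rise with no WHC effect.** Receipt rises by f x s. Adherence among all women rises by f x s x 0.56, if starters adhere at the plan's 56% and other women do not change.

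| f | s | Receipt (points) | Adherence (points) |
|---|---|---|---|
| 5% | 50% | 2.5 | 1.4 |
| 10% | 70% | 7.0 | 3.9 |
| 20% | 70% | 14.0 | 7.8 |
| 30% | 90% | 27.0 | 15.1 |

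Stopping reduces these. With f = 20%, s = 70% and 3% of women stopping, receipt rises by 14 - 3 = 11 points. For adherence to rise by 13 points at s = 70%, f must reach 0.13 / (0.70 x 0.56) = 33%.

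**3. Chance of a significant result with no WHC effect.** Simple tests stand in here for the planned regression models, and clustering is ignored.

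- Receipt, 14% starting and 3% stopping: SE = sqrt((0.17 - 0.11^2)/432) = 1.9 points, z = 0.11/0.0191 = 5.8. Rejection is nearly certain.
- Adherence, f = 20% with 0.40 of new women on ART and adherent at 6 months (close to 0.70 x 0.56 = 0.39): rise 8.0 points. The chance is 65% unpaired, and 88% paired with an assumed 10% changing each way for other reasons.
- Adherence, f = 10% with the same 0.40: rise 4.0 points, chances 22% and 40%.

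**4. Whether the design removes it.** Each cycle enrols and follows its own 120 women, and the text describes no patient-level measurement at a site before its WHC cycle. A calendar-time term does not absorb a change that follows time since diagnosis.

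**5. Whether viral load settles it.** The first routine test comes 6 months after ART start, although intervals may vary by clinic. A woman who starts after baseline would routinely have no on-treatment value at baseline, and her first result would fall due at or after the 6-month visit.

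**The case against.** **Many women may not be newly diagnosed.** The formative work found that many eligible women were not attending health facilities, so recruitment was extended into the community. ARV cards and medication were adopted as proof of status, so some entrants are already treated. The clinics also serve ART, TB and antenatal patients, and half the sample comes from rehab. This stands: f is unknown and may be small.

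**Routine uptake may be low.** The only ART coverage figure for a comparable group is 16%, from Pretoria, and the Background lists barriers to initiation. It may predate universal ART, but nothing in the article supports a particular s. This also stands. The rise falls in proportion to s.

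**ART receipt is not labelled effectiveness.** The Analysis section reserves that word for risk behaviors. However, adherence is in the pre-post list under Patient-level process and data collection, and receipt is analysed in a similar way.

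**A condensed article need not list instrument fields or strata.** That is fair, and the interview does cover ART use. The point rests instead on what is stated: the entry rule, the pre-post comparison and the offer of the WHC to all. Patient characteristics may enter as covariates, but a main effect of time since diagnosis would shift the level and leave the change between visits in place. A stratum or an interaction with visit is needed.

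**This is one instance of the missing control.** True, but it is a route that the stepped wedge's allowance for time trends does not cover, and it can be partly repaired cheaply.

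**Conclusion.** The concern holds in a limited form. The entry rule admits women at or near diagnosis, standard care would start some of them on ART, and the comparison cannot tell those starts from an effect of the WHC. Part, possibly much, of any rise in ART receipt, all-women adherence and viral suppression would arise this way. Women already on ART at baseline are less affected. Alcohol and drug use, condom use and violence are untouched by this route.

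The size rests on two assumed quantities: 2.5 to 27 points for receipt before stopping, and about 8 points for adherence in the middle case.

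Three stronger readings are not supported:

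- A reader might infer that standard care produces the whole rise. The article gives neither f nor s, so this is not shown.
- A reader might set the 14-point rise in receipt against the 13-point detectable difference. They are different outcomes; the matching adherence figure is 7.8 points.
- A reader might take earlier-diagnosed women as a clean test of the WHC. Untreated women among them are also entitled to ART, so their change remains uncontrolled.

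**What to change.** At baseline, record whether each woman is on ART. Where the proof document, clinic record or interview gives them, also record the dates of the first positive result and of ART start. Report the pre-post change in ART receipt and adherence separately for:

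1. women already on ART at baseline;
2. women off ART and recently diagnosed, for example within 6 months before baseline;
3. women off ART and diagnosed earlier.

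Do not attribute the rise in the second group to the WHC. Do not assign it wholly to standard care either, because the WHC itself includes referral and linkage. Describe the change in ART receipt as uncontrolled in every stratum.

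The cost is two date fields, confirmation that ART status is captured, and one stratified table. The strata will be smaller than the full sample. Some dates will be missing: ARV cards and medication may not show a first positive result, and Trial status reports that the electronic databases were out of date. Stratifying reduces this bias but does not supply the missing comparison.
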